**Figure 2 F2:**
[figure not shown]
Dry weight adjustment flow chart in the BCM arm.

#### Clinical events

##### Dialysis prescription change

Dialysis prescription may be changed according to clinical site’s standard practice including changes of dialyzer, blood flow rate, dialysate flow rate, frequency of dialysis, dialysis modality (conventional hemodialysis, high flux dialysis, hemofiltration, hemodiafiltration, and in combination of blood perfusion). Kt/V will remain not less than 1.2 despite dialysis prescription change. Dialysis prescription change is regarded as a clinical event and will be recorded.

##### Medications change

Medications (oral, subcutaneous and intravenous drug administration) can be changed according to clinical site’s practice, this including anti-hypertensives, active vitamin D and its analogues, erythrocyte stimulating agents (ESA), and iron supplements. Medications change is regarded as a clinical event and will be recorded.

##### New diagnosis

Any newly emerged diagnosis is regarded as a clinical event and will be recorded; hypotension and related clinical episode, hypertension and related clinical episode, pulmonary infection, diarrhea, angina pectoris, myocardial infarction, ischemic and hemorrhagic stroke, peripheral arterial occlusive disease, newly diagnosed neoplasm.

All deaths will be recorded as to date of death and cause.

##### Vascular access event

Vascular access bleeding, thrombosis or malfunction will be recorded.

##### Dry weight change

Each step of weight adjustment will be recorded.

##### Hospitalization

Hospitalization will be recorded, including diagnosis leading to hospitalization, date of hospitalization, length of stay, and outcome.

##### Abnormal laboratory value

If a procedure is performed to deal with abnormal laboratory value, the abnormal laboratory value is a clinical event and will be recorded.

##### Data censoring

The following participants are censored: (1) transfer to peritoneal dialysis, (2) renal transplantation, (3) becomes pregnant, (4) receives metal implantation, or any other reasons that make BCM measurement impossible, (5) limb amputation, (6) withdrawal of consent, (7) receives any forms of BIS measurement other than those specified by the trial protocol, (8) relocates to other clinical site, (9) investigator requests the participant be withdrawn from the study.

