#### Primary objective

The primary objective of the study is to compare incidence rate of a composite endpoint between BCM group and control group. Participants reach the primary endpoint if at least one of the following occurs: (1) death, (2) acute myocardial infarction, (3) cerebral thrombosis, (4) cerebral hemorrhage, (5) peripheral arterial occlusive disease. The diagnosis of endpoints will be made by the Endpoint Committee.

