##### Follow up data collection

Physical examination and urine volume collection will be performed every 2 months. CBC, routine laboratory data, and Kt/V will be obtained every 3 months. iPTH and hsCRP will be measured every 3 months. UCG will be performed every 12 months.

BCM measurement will be performed every 2 months in BCM arm, data will be recorded and provided to the care provider.

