#### Analytical method

##### Primary endpoint

The primary analysis will be an intent-to-treat analysis comparing composite endpoint between the BCM and the control arms. The intent-to-treat population is defined as all enrolled study participants. For this analysis, the follow-up time begins from the enrollment date to the composite endpoint, loss to follow-up, or end of study.

Multivariate Cox proportional hazards regression models will be used for analysis of the risk of death comparing BCM and control arms, with adjustment for age, sex, dialysis vintage, primary cause of ESRD, comorbid conditions, and other characteristics that may be associated with increased risk of death, such as inter-dialysis weight gain, hypertension and hsCRP.

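### The censoring list and the BCM-arm removal rule end follow-up for reasons that the intent-to-treat definition does not include, and amputation is censored with no stated precedence over peripheral arterial disease

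*Protocol article*

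**What the plan says.** Three sections of the Protocol article decide when a patient stops contributing to the primary comparison.

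- **Analytical method, Primary endpoint.** The analysis is intent-to-treat: "The intent-to-treat population is defined as all enrolled study participants". Time at risk is fixed as "the follow-up time begins from the enrollment date to the composite endpoint, loss to follow-up, or end of study".
- **Clinical events, Data censoring.** Nine reasons for censoring are listed. They include "4) receives metal implantation, or any other reasons that make BCM measurement impossible, (5) limb amputation", a participant who "receives any forms of BIS measurement other than those specified by the trial protocol", a move to another site, and "9) investigator requests the participant be withdrawn from the study". The others are transfer to peritoneal dialysis, transplantation, pregnancy and withdrawal of consent.
- **Dry Weight Adjustment Strategy.** Within the BCM-arm strategy, a patient who has the same adverse effect of dry weight change at two visits in a row is taken out of the study.

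Two further facts bear on this. The Primary objective counts "5) peripheral arterial occlusive disease" as an endpoint component. The Follow up data collection section states that "BCM measurement will be performed every 2 months in BCM arm"; the control arm has only its baseline measurement. The Study design section describes the trial as open label.

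**The concern.** Most of the listed reasons concern whether BCM can still be applied, or whether the protocol was kept. They do not stop anyone from learning whether the patient later dies or has an infarction, a stroke or peripheral arterial disease. If such patients are censored, they stay in the analysis population but their later events no longer count. The comparison then moves from the effect of assigning BCM guidance towards its effect while it is feasible and adhered to.

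Two features could turn this into bias rather than lost information.

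- **Imbalance by arm.** Follow-up BCM is scheduled in the BCM arm, so residual measurement problems would come to light mainly there. The removal rule for repeated adverse effects belongs to that arm's strategy and selects patients who tolerate it poorly. Investigator-requested withdrawal has no stated criteria, and investigators know the allocation.
- **Overlap with the endpoint.** Limb amputation is censored while peripheral arterial occlusive disease is an endpoint, and neither is given precedence.

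**Working it through.** **Step 1. Compare the rules.** The primary-endpoint section has three stopping points: event, loss to follow-up, end of study. Against these:

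| Reason | Among the three stopping points? | Composite still observable? |
|---|---|---|
| Withdrawal of consent | Can fairly be read as loss to follow-up | Not if it covers follow-up |
| Relocation to another site | Only if contact is truly lost | Usually |
| Metal implant, or BCM otherwise impossible | No | Yes |
| Limb amputation | No | Yes |
| Off-protocol bioimpedance | No | Yes |
| Investigator request | No | Generally |
| Repeated adverse effect (dry weight section) | No | Generally |
| Transplantation, peritoneal dialysis, pregnancy | No | Yes, but whether to count later events is an estimand choice |

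No section ranks one rule above another.

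**Step 2. Trace an amputation.**
- If arterial disease was diagnosed earlier, the endpoint has been reached and nothing is lost.
- If amputation is the first recorded sign, the patient may be censored instead of counted.
- If the patient had no prior event and dies afterwards, the death may go uncounted.

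**Step 3. Reproduce the plan's sample size.** Inputs from Sample size calculation: 40% v 32% at 3 years, α 0.05 (taken as two-sided), power 80%, equal arms. With pooled variance, p̄ = 0.36:

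n per arm = [1.96·√(2·0.36·0.64) + 0.8416·√(0.40·0.60 + 0.32·0.68)]² / 0.08² = 563.9, rounded up to 564, or 1128 in total. This matches the plan. The planned 1354 gives 677 per arm.

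**Step 4. Illustrate the size.** The documents give no censoring rates, so the share f of hidden events is assumed and shown as a range.

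*(a) Equal in both arms.* Rates become 0.40(1−f) and 0.32(1−f).

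| f | Power, 564 per arm | Power, 677 per arm |
|---|---|---|
| 0 | 80.0% | 86.7% |
| 5% | 76.8% | 83.9% |
| 10% | 73.4% | 80.9% |
| 20% | 66.1% | 74.0% |

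*(b) BCM arm only, no true effect.* p₁ = 0.40, p₂ = 0.40(1−f), d = p₁ − p₂, n = 677. The chance of a significant result favouring BCM is Φ[(d − 1.96·SE₀)/SE₁], with SE₀ = √(2p̄(1−p̄)/n) and SE₁ = √((p₁(1−p₁) + p₂(1−p₂))/n).

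For f = 5%: p₂ = 0.38, d = 0.02, p̄ = 0.39, SE₀ = 0.02651, SE₁ = 0.02650. Then (0.02 − 0.05196)/0.02650 = −1.206, and Φ = 11.4%.

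| f | Events hidden (677 × 0.40 × f) | Apparent relative risk | False result favouring BCM |
|---|---|---|---|
| 0 | 0 | 1.00 | 2.5% |
| 2% | about 5 | 0.98 | 4.9% |
| 5% | about 14 | 0.95 | 11.4% |
| 10% | about 27 | 0.90 | 32.8% |

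This compares proportions and scores a censored patient as event-free. In a Cox model the patient's later time at risk is removed as well, so the same hidden events distort the hazard ratio less. The hazard ratio is biased only so far as censored patients differ in risk from those who remain. The figures show sensitivity and are not a forecast.

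**The case against.** The defence has several sound points.

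- **The population is intact.** A reader might infer that the list removes patients from the intent-to-treat population. It does not: that population is all who enrol, and censoring leaves them in it. The conflict is with the stated end of follow-up and with the intent-to-treat principle.
- **Asymmetry is partial.** A reader might infer that inability to measure can be found only in the BCM arm. Implants, amputations and pregnancies are visible without a BCM reading, and clinical events and hospital stays are recorded in both arms. Only the residual wording about other reasons is likely to be found mainly in the BCM arm.
- **Not every reason sits near an event.** A reader might count a coronary or peripheral stent as a metal implant. The document does not mention stents; its examples of metallic prosthesis, in the exclusion criteria, are contraceptive devices and artificial joints. Off-protocol bioimpedance has no evident link to imminent events. The link between amputation and arterial disease is clinical inference.
- **An amputation need not erase an endpoint.** Disease diagnosed beforehand already counts, and nothing says that the event takes the date of the committee's decision.
- **Power has some cushion.** With 677 per arm, hiding 10% of events equally still leaves 80.9%. That cushion is the plan's allowance for loss to follow-up, however, so both draw on it.

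It might also be said that an article condenses a fuller protocol. That would excuse silence, but here the article states rules that disagree. The unranked rules, the one-arm removal rule and the missing precedence for amputation all stand.

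**Conclusion.** The point holds as an unresolved conflict between three stated rules. Followed as written, the censoring list and the removal rule discard later composite events on grounds of BCM feasibility, adherence or tolerance. That moves the primary estimate towards an on-protocol effect, and the loss may differ by arm. For amputation, the loss is confined to cases where it is the first sign of arterial disease or where death follows without a prior event.

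The size is unknown. If events were hidden in the BCM arm alone, about 5 to 27 of them would be enough to raise the one-directional false-positive rate from 2.5% to between 4.9% and 32.8%. This rests on the assumed shares, wholly one-sided hiding and a comparison of proportions. The documents do not support a claim that such an imbalance will occur, nor a firm direction of bias.

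The matter should be settled while follow-up is running, because events that were never recorded cannot be recovered at analysis.

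**What to change.** Reconcile the Data censoring, Dry Weight Adjustment Strategy and Primary endpoint sections as follows.

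1. In the primary analysis, keep following and counting composite events in all randomised patients after a metal implant, inability to measure BCM, amputation, off-protocol bioimpedance, relocation, investigator request or removal for a repeated adverse effect.
2. Censor only at withdrawal of consent to follow-up, true loss to follow-up or end of study.
3. State explicitly how transplantation, transfer to peritoneal dialysis and pregnancy are handled. This is an estimand choice for the sponsor.
4. Send every limb amputation to the existing Endpoint Committee, to decide whether it is a peripheral arterial event before any censoring applies.
5. Use the present censoring list only in a per-protocol sensitivity analysis.

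This concerns outcome follow-up and analysis only. It takes no position on when treatment or BCM guidance should stop. The required 1128 is unchanged. The cost is revised wording, continued event follow-up of patients who leave BCM guidance or change site, and some dilution of the effect from patients no longer guided by BCM.

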#### Safety issue

The clinical use of BIS method had been approved by State of Food and Drug Administration (SFDA). As one form of BIS method, BCM device is widely used in Europe. BIS inject weak alternating current into human body, which cause no harm to human body.

### Statistical analysis

#### Study hypotheses

This study is designed to test the primary hypotheses that patients receiving BCM guided fluid management have lower rate for the composite endpoint of mortality, cardiovascular and cerebrovascular events compared with patients receiving fluid management according to clinical site’s standard care. The secondary hypotheses that will be tested are that patients receiving BCM measurement have (1) lower left ventricular thickness and higher left ventricular ejection fraction, (2) better blood pressure control, (3) less anti-hypertensive medication, (4) lower hospitalization rate.

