**Methods:**

This is a multicenter, prospective, randomized, controlled trial. More than 1300 participants from 16 clinical sites will be included in the study. The enrolment period will last 6 months, and minimum length of follow-up will be 36 months. MHD patients aged between 18 years and 80 years who have been on MHD for at least 3 months and meet eligibility criteria will be invited to participate in the study. Participants will be randomized to BIA arm or control arm in a 1:1 ratio. A portable whole body bioimpedance spectroscopy device (BCM—Fresenius Medical Care D GmbH) will be used for BIA measurement at baseline for both arms of the study. In the BIA arm, additional BCM measurements will be performed every 2 months. The primary intent-to-treat analysis will compare outcomes for a composite endpoint of death, acute myocardial infarction, stroke or incident peripheral arterial occlusive disease between groups. Secondary endpoints will include left ventricular wall thickness, blood pressure, medications, and incidence and length of hospitalization.

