#### Secondary objectives

Secondary objectives are to compare the following indices between BCM arm and control arm: (1) left ventricular thickness and left ventricular ejection fraction, (2) Pre-HD and post-HD blood pressure, (3) anti-hypertensive medication, (4) hospitalization rate.

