#### Exclusion criteria

Candidates meeting any one of the following criteria will not be eligible to be included in the study: (1) acute infection within prior month, (2) active rheumatic disease, or current receipt of cortical steroid or cytotoxic medication, (3) uncontrolled neoplasm, (4) acute myocardial infarction within prior month, (5) congestive heart failure (NYHA 3 – 4), (6) stroke within 3 prior months, (7) metallic prosthesis (contraceptive device, artificial joint), (8) amputation, (9) female of childbearing age who has a pregnancy plan, or is pregnant, or is breast feeding, (10) having a plan to reduce dialysis frequency, (11) having a renal transplantation plan or planning to transfer to peritoneal dialysis within 3 years, (12) participating or planning to participate in other clinical trials which would confound the current study.

Candidates meeting inclusion and exclusion criteria will be included in the study after providing informed consent. Study approval is obtained from the Institutional Review Board, Peking University First Hospital. This study is registered on ClinicalTrial.gov and has the identification number NCT 01509937.

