#### Data collection

Summary of data collection is listed in Table
1.

**Table 1 T1:** BOCOMO study schedule of data collection

**Item**	**Baseline frequency**	**Follow up frequency**
Demographic information	Once	-
ESRD history^1^	Once	-
Comorbidity^2^	Once	-
Physical examination^3^	Once	Every 2 months
Timed urine collection^4^	Once	Every 2 months
CBC^5^	Once	Every 3 months
Routine laboratory data^6^	Once	Every 3 months
Kt/V	Once	Every 3 months
iPTH	Once	Every 3 months
hsCRP	Once	Every 3 months
UCG	Once	Every 12 months
BCM measurement	Once	Every 2 months in BCM arm
Dialysis prescription change^7^	Once	Throughout the study period
Medication change^8^	Once	Throughout the study period
New clinical event^9^	-	Throughout the study period

Abbreviation: BOCOMO study, body composition monitor study; ESRD, end stage renal disease; CBC, complete blood count; Kt/V, calculated using Daugirdas single pool equation; iPTH, intact parathyroid hormone; hsCRP, high sensitive C-reactive protein; UCG, ultrasonic cardiograph.

^1^ESRD history includes cause of ESRD, date of first dialysis, type of vascular access.

^2^Detailed history of comorbidity will be assessed, including vascular access events.

^3^Physical examination includes body weight, blood pressure, heart rate, edema, pulmonary rale, before and after hemodialysis session.

^4^24 hours urine volume collected the day before dialysis session will be recorded.

^5^Consists of hemoglobin, white blood cell count, platelet count.

^6^Consists of albumin, pre-Albumin, creatinine, urea, potassium, sodium, chloride, calcium, phosphate, bicarbonate, alkaline phosphatase (ALP), glucose, triglycerides, total cholesterol, low density lipoprotein, high density lipoprotein, brain natriuretic peptide (BNP).

^7^Any dialysis prescription change throughout the study period will be recorded.

^8^Any medication change throughout the study period will be recorded.

^9^Any new clinical event throughout the study period will be recorded, including hospitalization, new diagnosis, vascular access related event, treatment of abnormal laboratory value, dry weight adjustment.

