##### Secondary endpoint

The following 3 secondary endpoints will be compared between BCM and control arms using grouped t-test, and within group trend will also be analyzed: (1) left ventricular thickness and left ventricular ejection fraction, (2) pre-HD and post-HD blood pressure, (3) anti-hypertensive medication.

The secondary endpoint of incident rate of hospitalization will be compared between BCM arm and control arm using general Linear Model with Poisson regression.

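### Left ventricular wall thickness alone is an ambiguous marker of muscle regression in a trial that changes fluid volume; add left ventricular mass and report cavity diameter beside it

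*Protocol article*

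**What the plan says.** The article names the same two cardiac measures in three places. Secondary objectives lists "1) left ventricular thickness and left ventricular ejection fraction, (2) Pre-HD and post-HD blood pressure". Study hypotheses fixes the favourable direction: "1) lower left ventricular thickness and higher left ventricular ejection fraction". Under Analytical method, the Secondary endpoint section says that these measures, with blood pressure and antihypertensive medication, "will be compared between BCM and control arms using grouped t-test, and within group trend will also be analyzed". The abstract is shorter still: "Secondary endpoints will include left ventricular wall thickness, blood pressure, medications".

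Ejection fraction is a functional measure, so thickness is the only structural one. Left ventricular mass, mass index, cavity diameter and volume are not named as endpoints anywhere. The data come from echocardiography at baseline and then yearly: "UCG will be performed every 12 months".

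Under Dry Weight Adjustment Strategy, dry weight in the BCM arm is moved toward the device's value, which may be above or below the current one.

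**The concern.** Wall thickness depends on two things: how much muscle there is, and how large a cavity it surrounds. The intervention acts on fluid volume and so may act on cavity size directly.

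Where dry weight is lowered and the cavity shrinks, the wall reads thicker unless enough muscle regresses to offset it. Where dry weight is raised and the cavity fills, the wall reads thinner with no regression at all. The first would count against the stated hypothesis and the second in its favour, and neither reading would say what had happened to the muscle.

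What is at stake is the interpretation of one secondary result. Thickness could show no difference, or one of the wrong sign, despite a modest true regression, and the named endpoints include no second structural measure to resolve it. The choice of variable and its favourable direction are stated outright and consistently, so this is a stated design choice and not detail left out of a condensed article.

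**Working it through.** **Inputs.** From the article: the endpoint, its favourable direction, adjustment of dry weight in both directions, the planned total of 1354 and the 20% loss allowance. The article gives no cavity size, wall thickness, standard deviation or expected change, and no planned figure for this endpoint that could be reproduced. These are therefore assumptions: cavity diameter D = 5.2 cm and both walls w = 1.1 cm.

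**Formula (cube formula, cm and g).** Mass = 0.8 × 1.04 × [(D + 2w)³ − D³] + 0.6.

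Baseline: (5.2 + 2.2)³ − 5.2³ = 405.224 − 140.608 = 264.616, so mass = 0.832 × 264.616 + 0.6 = 220.8 g.

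**Step 1: wall thickness for a given cavity and mass.** Solving for w gives w = {[(Mass − 0.6)/0.832 + D³]^(1/3) − D}/2. Results in mm, against a baseline wall of 11.0:

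| Cavity (mm) | Mass unchanged | Mass −5% | Mass −10% |
|---|---|---|---|
| 52 (no change) | 11.00 | 10.59 | 10.17 |
| 51 (−1) | 11.26 | 10.84 | 10.42 |
| 50 (−2) | 11.52 | 11.10 | 10.67 |
| 49 (−3) | 11.79 | 11.36 | 10.93 |
| 54 (+2) | 10.51 | 10.11 | 9.70 |

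A 5% regression reads as a thinner wall with a 1 mm cavity reduction, but as a thicker one with 2 or 3 mm. A 10% regression always has the right sign, but its size shrinks from −0.83 mm (cavity unchanged) to −0.07 mm (cavity 3 mm smaller). A cavity 2 mm larger gives an apparent benefit of about 0.5 mm with no change in muscle.

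**Step 2: regression needed before the wall reads thinner.** Hold w at 1.1 cm and compare mass at the smaller cavity with 220.8 g:

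- 51 mm: 213.9 g, a fall of 3.1%
- 50 mm: 207.1 g, a fall of 6.2%
- 49 mm: 200.5 g, a fall of 9.2%

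**Step 3: other starting values.** With cavities of 46–55 mm, walls of 10–14 mm and muscle volume held fixed, the wall rises by 0.24–0.31 mm if the cavity diameter falls 2%, by 0.61–0.79 mm if it falls 5%, and by 1.26–1.63 mm if it falls 10%. The pattern does not depend on the 52/11 mm example.

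**Step 4: could the t-test pick up a shift of this size?** After a 20% loss, 1354 × 0.8 / 2 ≈ 542 per arm. The detectable mean difference at 80% power and two-sided 5% is (1.960 + 0.842) × SD × √(2/n). With an assumed SD of 1.5–2.5 mm this is 0.26–0.43 mm at n = 542. Deaths will also reduce the number with a late echocardiogram; at an assumed n = 300 per arm it is 0.34–0.57 mm. Mean between-arm shifts at the upper end of Step 1 would be detectable, and those from a 1 mm cavity change mostly would not.

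**The case against.** The strongest reply is that the trial compares arm means, and the cavity contrast between arms may be small. Participants enter with a dry weight their doctor considers adequate, controls also have dry weight adjusted under usual practice, all participants are taught to limit weight gain between sessions, and BCM-arm adjustment goes both ways, so cavity effects partly cancel. This stands. Nothing in the article supports a mean difference of 3 mm, and the per-patient figures above should not be read as predicted arm differences. Cancellation also leaves the ambiguity in place: a null result would still not show whether muscle had regressed.

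It can also be said that the hypothesis is literally about thickness, so the endpoint tests it, and that thickness is a defensible choice where hypertension is one of the harms of excess fluid. Both are correct. The criticism is of what a thickness result says about regression.

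A reader might infer three stronger points that the document does not support:

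- **That fluid removal thickens the wall as a rule.** It does so only if cavity shrinkage outweighs regression, and no figure in the article settles that.
- **That ejection fraction has little room to rise because of the exclusion "5) congestive heart failure (NYHA 3 – 4".** NYHA class grades symptoms. The exclusion sets no ejection-fraction limit, and no baseline value is given.
- **That the timing of echocardiography within the dialysis cycle is missing.** A full protocol would normally carry that detail, and it is not shown here.

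**Conclusion.** The point holds as one of interpretation. Thickness alone cannot distinguish muscle regression from cavity change in a trial whose intervention may alter the cavity. Under the assumed 52/11 mm geometry, the sign is wrong only when regression is below about 3%, 6% or 9% for a cavity 1, 2 or 3 mm smaller; above those thresholds the sign is right but the effect is understated. A larger cavity produces the opposite error.

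The cavity, wall and SD values are all assumptions, and the size of any cavity difference between arms is unknown. The consequence is confined to one secondary endpoint. The primary composite, its sample size and its analysis are untouched. The change is worth making because it is cheap and this is the only structural cardiac endpoint named.

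**What to change.** In Secondary objectives, Study hypotheses and the Secondary endpoint section, add left ventricular mass as the structural endpoint used to judge regression. Calculate it from the annual echocardiogram already planned, using septal wall, posterior wall and end-diastolic cavity diameter. Index it to a measure the intervention does not change, such as height; body weight and surface area are less suitable because the intervention alters weight. Keep wall thickness and report it with cavity diameter as components of mass. Replacing thickness altogether is not necessary.

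The cost is one more derived variable, and recording of cavity diameter if the case report form does not already hold it. No extra visit or examination is needed. One limitation remains: calculated mass also uses the cavity measurement, so it too must be read beside cavity diameter.
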